#### 6.1.4.1. Diarrhoea Management

Diarrhea is an expected clinically significant adverse event when treating patients with anti-CTLA4 investigational drugs. The diarrhea may be severe, may require hospitalization, and may result in intestinal perforation. The following algorithm is recommended for the treatment of patients who develop diarrhea while on trial:

| **Diarrhea Treatment Algorithm** | |
| --- | --- |
| **Diarrhea Severity** and Duration** | **Recommendation** |
| Grade 1 less than or equal to 14 days | • Consider use of probiotics  • Follow Diarrhea Management Guidelines including *C. difficile* titer, stool tests, empiric loperamide, oral fluid replacement  • Consider use of olsalazine, or masalamine |
| Grade 1 more than 14 days or Grade 2 of any duration not responsive to loperamide | • Consider use of probiotics  • Evaluation of severity by clinician familiar with CP-675,206-related diarrhea  • Consider IV fluids if indicated  • Consider use of budesonide, olsalazine, or masalmine  • Consider use of steroids* |
| Grade 3 or Grade 4 for any duration  Or  Any grade & duration associated with evidence of severe enterocolitis including bleeding, fever, pain or other signs/symptoms | • Consider use of probiotics  • Evaluation by clinician familiar with CP-675,206-related diarrhea  • Consider inpatient hospitalization for IV fluids, monitoring  • Consider use of budesonide, olsalazine, or masalamine  • Consider use of steroids* |
| ***** Response of diarrhea to steroids has been reported for a similar experimental drug that targets CTLA4. Example: oral or intravenous dexamethasone up to 4 mg every 4 hours  ** Grade 1 = increase of < 4 stools/d over baseline  Grade 2 = increase of 4-6 stools/d over baseline  Grade 3 = increase of ≥ 7 stools/d over baseline  Grade 4 = life-threatening consequences (e.g. hemodynamic collapse) | |

#### 6.1.4.2. Diarrhoea Prophylaxis

To date there is no data or evidence indicating effectiveness of prophylactic therapy for prevention of treatment emergent diarrhea secondary to CP-675,206. However, prophylaxis may be considered. If prophylaxis is used, one of the following drugs would be recommended:

1. • Probiotics (active cultures of beneficial bacteria which can be found in some brands of yogurt or in supplements) have been shown to be effective with other types of diarrhea, including ulcerative colitis, in clinical trials. Probiotics might prevent diarrhea by replacing gut bacteria with more benign strains, thereby decreasing the overactive T cell response to gut flora. This approach is not expected to present a risk to the patient.
2. • Mesalomine (Asocal) is an anti-inflammatory drug, and it takes several days to be effective. It may be considered for prophylactic use, but there is currently no data to support its use.

Loperamide treats only the symptoms of diarrhea and not the underlying cause. It should not be used prophylactically.

Steroids can be used to treat severe or prolonged diarrhea due to CP-675,206, but should not be used prophylactically.

### **6.1.5. Management of Hypersensitivity Reactions**

In case of hypersensitivity reactions, the Investigator should institute treatment measures deemed medically appropriate. The following treatment recommendations may be applicable and can be adopted at the Investigator’s judgment:

| **Hypersensitivity reaction:** | **Treatment recommendations:** |
| --- | --- |
| CTCAE v.3.0 Grade 1 Allergy (transient flushing or rash, drug fever <38°C) | • Supervise at the bedside. |
| CTCAE v.3.0 Grade 2 Allergy (urticaria, drug fever ≥ 38°C, and/or asymptomatic bronchospasm) | - 1. • Interrupt the infusion of CP-675,206 and disconnect infusion tubing from patient;   2. • Administer IV antihistamines (diphenhydramine, 25-50 mg, and ranitidine, 50 mg, or cimetidine, 300 mg);   3. • After recovery of symptoms, resume the infusion at half the initial infusion rate. If no further symptoms appear, complete the administration of the dose. If symptoms reappear, stop infusion and discontinue patient from the trial. |
| CTCAE v.3.0 Grade 3 or 4 Allergy (symptomatic bronchospasm requiring parenteral medication(s) with or without urticaria; allergy-related edema/angioedema; hypotension; anaphylaxis) | - 1. • Stop the infusion of CP-675,206 and disconnect infusion tubing from patient;   2. • Administer epinephrine (1:10,000) in 3.5 to 5 mL IV boluses (no more than 6 doses);   3. • Administer IV antihistamine (diphenhydramine 50 mg IV push);   4. • If wheezing persists: 0.35 mL of nebulized albuterol or other bronchodilators;   • Consider methylprednisolone 30 to 60 mg IV push, which may prevent recurrent or ongoing reactions; |

## **6.2. CP-675,206 Drug supply**

### **6.2.1. CP-675,206 - Preparation and Dispensing**

It is recommended that appropriate site pharmacy personnel (or equivalent) refer to the most current version of the Dosing and Administration Instructions (DAI) for detailed instructions on the preparation and administration of CP-675,206. It is suggested that all manipulations are carried out in a laminar flow cabinet using aseptic technique for maximum patient protection. Only the necessary materials should be present in the working area during each preparation step.

### **6.2.2. Administration**

The investigational drug will be administered as specified in the most current version of the DAI. CP-675,206 administration will take place in the Princess Margaret Hospital chemo daycare unit which has extensive experience with drug administration and management of toxicities.

Although CP-675,206 is a fully human monoclonal antibody, immunogenicity remains a possibility, and thus acute hypersensitivity reactions such as urticaria, pruritus, laryngeal edema, angioedema, bronchospasm, respiratory distress, nausea, vomiting, crampy abdominal pain, acute back pain, fever, diarrhea, hypotension and fatal anaphylactic shock, as well as subacute reactions, are also possible. The patients’ blood pressure, heart rate, and temperature should be recorded prior to treatment and monitored, as needed during drug infusion and for approximately 1 hour post- infusion.

Medications to treat hypersensitivity reactions should be available, such as IV saline, acetaminophen, and emergency drugs, including subcutaneous epinephrine, diphenhydramine, methylprednisolone, and nebulized albuterol.

## **Concurrent Medication(s)**

Once a patient begins trial treatment, the addition of any other concurrent cancer treatment (including cytotoxic, hormonal, homeopathic, or immunologic therapy) might confound the assessment of safety and efficacy and, therefore, is not recommended. Such concurrent treatments should be delayed for 12 weeks following CP-675,206 dosing if clinically acceptable. Due to the unknown potential for drug-drug interactions, the use of any unapproved, naturalistic, homeopathic, or holistic therapies is disallowed. Medication intended solely for supportive care (eg, analgesics, antibiotics, antiemetics, antidiarrheals, or antidepressants) may be used at the investigator’s discretion. During the trial, patients may require immunosuppressive drugs such as corticosteroids for management of underlying disease, treatment-related toxicity, or unrelated conditions.

Steroid use for no longer than 10 days is permitted. However low dose daily steroid use (5 mg of prednisone or equivalent daily) and topical and inhaled corticosteroids in standard doses are allowed.

It is highly recommended that patients not be exposed to anti-infective vaccinationswhile participating in the trial (i.e. within the minimum observation period of 12 weeks following CP-675,206 dosing), given that the effect of the vaccination has not been explored under conditions of CTLA4 blockade. Any such vaccinations will be recorded on the Concomitant Medication CRF.

## **Salvage Therapy**

Patients who discontinue treatment on this trial may receive subsequent therapy based on the judgment of the treating physician.

## **Additional cycles**

Patients that exhibit a clinical response following CP-675,206 dosing may be eligible to receive a subsequent dose of CP-675,206 90 days following the first dose. Additional dosing will be based on the judgment of the treating physician and after communication with Pfizer.

# 7. TRIAL PROCEDURES

The minimum required screening, on-study and follow-up evaluations are summarized in the following sections. Other parameters and/or increased frequency of examinations or clinical follow-up may be needed based on the findings during the trial.

Informed consent must be obtained from each patient being considered for the trial before any protocol-specified procedure is performed. In the event of scheduling conflicts, trial evaluations will take place on the designated day ± 3 days.

## **Pre-trial Assessments**

The minimum required screening procedures must be performed within 14 days before enrollment (unless otherwise specified). Screening procedures must be fully documented in the patient’s medical record and transferred to the CRF. Pretrial Assessments are outlined below:

**Table 1. Pre-trial assessments**

| **Assessment/Test** | **Within 72 Hours** | **Within 5 days** | **Within 14 Days** | **Within 28 Days** |
| --- | --- | --- | --- | --- |
| Obtain Informed Consent |  |  | X |  |
| Medical History1 |  |  | X |  |
| Baseline Signs & Symptoms2 |  |  | X |  |
| Enrollment |  | X |  |  |
| Height |  |  | X |  |
| Weight |  |  | X |  |
| Physical Exam, including vital signs and clinical signs of autoimmunity3 |  |  | X |  |
| Review of Concomitant Medications4 |  |  | X |  |
| ECOG status |  |  | X |  |
| ECG |  |  | X |  |
| Pregnancy Test (serum or urine) for women of childbearing potential (WOCBP)5 | X |  |  |  |
| Hematology6 |  |  | X |  |
| Serum Chemistry7 |  |  | X |  |
| Total IgG |  |  | X |  |
| Microscopic Urinalysis8 |  |  | X |  |
| Thyroid Function9 |  |  | X |  |
| HIV, Hepatitis screening10 |  |  | X |  |
| HLA Typing |  |  | X |  |
| Adverse Events |  |  | X |  |
| Tumor Imaging (CT, MRI)11 |  |  |  | X |

**1.** Includes review of systems, oncologic history and general medical history of all disease processes (active or resolved), and concomitant illnesses. Disease characteristics include diagnosis, date of diagnosis, cytology or histology, stage at time of trial entry, and breast cancer treatment history.

**2.** The Investigator should describe any signs and symptoms at presentation reported by patients during the 14 days prior to the initial dose of CP-675,206. Patients should be questioned about visual symptoms. Any patient who is experiencing symptoms suggestive of uveitis or melanoma-associated retinopathy (eg eye pain or redness, sensitivity to light or glare, blurred vision, floaters, night blindness, or visual field defects) should be evaluated by an ophthalmologist to rule out these conditions.

**3.** The physical exam should be performed by an Investigator at baseline, and a physician or designee may perform subsequent assessments, as appropriate. Vital signs include temperature, blood pressure, heart rate while sitting

**5.** Must be negative within 72 hours prior to the initial dose of CP-675,206.

**4.** All concomitant medications taken within 14 days need to be documented and recorded (including start and stop dates, as appropriate) on the patient CRF.

**6.** Hemoglobin, WBC with 5-part differential (percent and absolute values), platelet count.

**7.** Calcium, chloride, total protein, potassium, random glucose, sodium, blood urea nitrogen/BUN, creatinine, AST/SGOT, ALT/SGPT, alkaline phosphatase/ALP, lactic acid dehydrogenase/LDH, amylase, lipase, albumin, total bilirubin

**8.** Collect urine for Urinalysis [must include: 1) microscopic analysis of urinary sediment and 2) analysis for protein, glucose, and blood (other, as indicated)].

**9.** Thyroid stimulating hormone (TSH), T3, T4.

**10.** Refer to Exclusion Criteria.

**11.** Documentation of Baseline target and non target lesions by imaging techniques or by measurement of clinical lesion(s) must be performed within 28 days prior to dosing. The method of tumor assessment (CT, MRI) and tumor sites are to be consistent from baseline to the end of the study.

## **7.2. On-Trial Assessments**

One to two days prior to CP-675,206 dosing (i.e. day 1 or 2 of radiation treatment), the following should be done and results available prior to day 3 CP-675,206 administration:

1. **1.** All women of childbearing potential must have a negative serum or urine pregnancy test within 72 hours prior to the initial dose of CP-675,206 (see “Pre-trial assessments”).
2. **2.** Collect urine for Urinalysis [must include: 1) microscopic analysis of urinary sediment and 2) analysis for protein, glucose, and blood (other, as indicated)].
3. **3.** Blood draws for hematology, serum chemistry, autoantibodies.
4. **4.** Other blood draws will also be done but results do not need to be available prior to CP-675,206 administration (HAHA, immune monitoring).

On the day of CP-675,206 dosing, the following should be done prior to the dose of CP-675,206:

1. **1.** Baseline Signs and Symptoms
2. **2.** Review of Concomitant Medications
3. **3.** ECOG Performance Status/Weight
4. **4.** Clinical Assessments/Vital Signs (temperature, blood pressure while sitting, heart rate)
5. **5.** Physical Exam
6. **6.** Review of visual symptoms
7. After the assessments listed above are performed and safety labs reviewed, investigational drug may be administered intravenously. During infusion, vital signs will be monitored and treatment-emergent adverse events will be recorded.

All other tests and assessments to be performed during treatment with CP-675,206 are outlined in the following table.

**Table 2. On-trial assessments**

**Test/Assessment: Study Day Number:**

|  | D1 | D2 | D3 | D4 | D5 | D8  (1w) | D15  (2w) | D22  (3w) | D29  (4w) | D43  (6w) | D57 (8w) | D71  (10w) | D85  (12w) |
| --- | --- | --- | --- | --- | --- | --- | --- | --- | --- | --- | --- | --- | --- |
| Weight |  |  | X |  |  | X | X | X | X | X | X | X | X |
| Physical Exam, including signs of autoimmunity |  |  | X1 |  |  | X | X | X | X | X | X | X | X |
| ECOG status |  |  | X1 |  |  | X | X | X | X | X | X | X | X |
| Hematology2,3,4 | X |  |  |  |  | X | X | X | X | X | X | X | X |
| Serum Chemistry3,4,5 | X |  |  |  |  | X | X | X | X | X | X | X | X |
| Microscopic or Dipstick Urinalysis3,4,6 | X |  |  |  |  | X | X | X | X | X | X | X | X |
| Thyroid Function3,4,7 |  |  |  |  |  |  |  |  | X |  |  |  | X |
| Autoantibody Panel3,4,8 | X |  |  |  |  |  |  |  | X |  |  |  | X |
| Human anti-human antibody (HAHA)9 | X |  |  |  |  |  |  |  | X |  |  |  | X |
| Radiation10 | X | X | X | X | X |  |  |  |  |  |  |  |  |
| CP-675,206 Administration |  |  | X |  |  |  |  |  |  |  |  |  |  |
| Immune Monitoring11 | X |  |  |  |  | X | X |  | X |  | X |  | X |
| Blood specimen for genomic analysis12 | X |  |  |  |  |  |  |  |  |  |  |  |  |
| AE Monitoring13 | X | X | X | X | X | X | X | X | X | X | X | X | X |
| Tumor Imaging (CT, MRI)14 |  |  |  |  |  |  |  |  |  |  | X |  |  |

**1.** Tests performed/specimens drawn prior to dosing with CP-675,206.

**2.** Hemoglobin, WBC with 5-part differential (percent and absolute values), platelet count

**3.** Clinically significant abnormalities should be reported as Adverse Events in the CRF.

**4.** Assessments may be performed within 24 hours of the designated timepoints.

**5.** Calcium, chloride, total protein, potassium, random glucose, sodium, blood urea nitrogen/BUN, creatinine, AST/SGOT, ALT/SGPT, alkaline phosphatase/ALP, lactic acid dehydrogenase/LDH, amylase, lipase, albumin, total bilirubin

**6.** Complete urinalysis (with microscopic analysis of centrifuged sediment for casts or other abnormalities); performed at baseline. In subsequent evaluations, dipstick urine testing is allowed in lieu of microscopic analysis, however, microscopic analysis must be performed if dipstick results are abnormal.

**7.** Thyroid stimulating hormone (TSH), T3, T4. Thyroid function tests are also done as part of the pre-trial assessments (within 14 days before treatment begins).

**8.** The autoantibody panel will include antinuclear antibodies (ANA), antineutrophil cytoplasmic antibodies (ANCA), anti-DNA antibody (SS and DS), Rh factor (RhF), antithyroglobulin, anti liver-kidney microsomal (LKM), anti-islet-cell, antibodies to Ro (SSA) and to La (SSB) and antiphospholipid and/or other autoantibody tests.

**9.** Human anti-human antibody may be done at the Investigator’s discretion.

**10.** A total of 2000cGy to be delivered in 5 daily fractions using 6-18 MV photons.

**11.** Immune monitoring will be done using peripheral blood obtained by phlebotomy. PBMC and serum will be isolated and cryopreserved.

**12.** DNA extraction and banking for genomic evaluation.

**13.** Adverse event assessment to be performed continuously throughout the trial. Treatment-related adverse events will be followed until they resolve to baseline or Grade 1 or until the treating physician determines that they are irreversible.

**14.** Patients with measurable disease will be assessed by imaging every 8 weeks until progression (range 6-8 weeks). If a response is seen at week 8, the imaging will be repeated 4 weeks later. The same method of assessment and the same technique should be used for repeated measurements.

## **7.3. Follow-up Visits**

### **7.3.1. Treatment-Related Adverse Event Follow-Up**

Approximately one month (30 days) after the end of treatment evaluation, a follow up visit is required. Such on going AEs should be followed to ensure that they have resolved, returned to baseline, or are deemed irreversible by the Investigator. If there is evidence of continuing CP-675,206-related toxicity, the patient should continue to be followed at intervals deemed medically appropriate by the Investigator. The required (minimum) laboratory tests and observations for these patients are the following:

- 1. Physical exam, including signs of autoimmunity.
  2. If clinically warranted: hematology, serum chemistry, urinalysis, autoantibody panel.
  3. Treatment-related adverse events will be followed to resolution or until the treating physician determines that they are irreversible.

Additional observations and laboratory tests should be performed according to medical need.

### **7.3.2. Disease Progression Follow-Up**

All patients will be followed for disease progression (if prior SD, PR, or CR) or until the start of a new therapeutic regimen for breast cancer, whichever comes first. This information will be recorded in the CRF. It is understood that not all patients will be available for continued clinic visits; however, every attempt should be made to collect progression date and subsequent therapy (start of therapy).

### **7.3.3. Survival Follow-Up**

All patients should continue to be followed every 3 months when possible for up to 1 year. It is understood that not all patients will be available for continued clinic visits; however, every attempt should be made to access survival information (disease status, alive or dead, and date of death). This information may be obtained by telephone interview if the patient is unable to visit the clinic.

## **Patient Withdrawal**

Patients may withdraw from the trial at any time at their own request, or they may be withdrawn at any time at the discretion of the Investigator for safety, behavioral, or administrative reasons. If a patient does not return for a scheduled visit, every effort should be made to contact the patient. In any circumstance, every effort should be made to document patient outcome, if possible. The Investigator should inquire about the reason for withdrawal, request the patient to return all unused investigational product(s), request the patient to return for a final visit, if applicable, and follow-up with the patient regarding any unresolved adverse events.

If the patient withdraws from the trial and also withdraws consent for disclosure of future information, no further evaluations should be performed and no additional data should be collected. The Investigator may retain and continue to use any data collected before such withdrawal of consent.

A discontinuation occurs when an enrolled patient ceases participation in the trial, regardless of the circumstances, prior to completion of the protocol. The Investigator must determine the primary reason for discontinuation:

1. **1.** Withdrawal due to adverse event. When a discontinuation is due to a serious adverse event (SAE), the serious adverse event must be reported in accordance with the reporting requirements.
2. **2.** Patients may decide to withdraw from the trial at any time. Patients who withdraw from treatment should be followed for survival, and their subsequent treatments should be recorded.
3. **3.** Patients must be discontinued if the Investigator believes it to be in the patient’s best interest to begin chemotherapy or biological therapy for his/her disease.
4. **4.** The Investigator should withdraw the patient at any time if he/she believes it is in the patient’s best interest to do so.

The final evaluation required by the protocol will be performed at the time of trial discontinuation. The Investigator will record the reason for trial discontinuation and provide or arrange for appropriate follow-up (if required) for the patient.

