# 1. SUMMARY

Patients with inoperable locally recurrent or metastatic breast cancer requiring local radiotherapy will be given local radiation to one tumor site and systemic CP-675,206. Successive cohorts of subjects will be given escalating doses of CP-675,206 in order to determine the maximum tolerated dose of CP-675,206 when given in combination with radiation. The primary endpoint will be toxicity. The secondary endpoints will be clinical and immunological responses. This trial is being conducted as a prelude to a planned phase II trial of CP-675,206 in combination with radiation in metastatic breast cancer.

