## **2.2. CP-675,206**

*Additional information can be found in the CP-675,206 Investigator’s Brochure.*

CP-675,206 is a fully human monoclonal antibody (mAb). It binds to the CTLA4 molecule, which is expressed on the surface of activated T lymphocytes and T regulatory cells. The binding of CTLA4 to its target ligands (B7-1 and B7-2) provides a negative regulatory signal, which limits T-cell activation. CP-675,206 antagonizes binding of CTLA4 to B7 ligands and enhances human T-cell activation as demonstrated by increased cytokine (interleukin-2, interferon-) production in vitro in whole blood or peripheral blood mononuclear cell cultures. CP-675,206 is thought to stimulate patients’ immune systems to attack their tumors by blocking the negative regulatory signal of CTLA4.

There is emerging evidence that T regulatory cells may play a role in cancer progression or may present a barrier to immunotherapy (2). Increased numbers of T regulatory cells with an immune suppressive phenotype have been observed in the peripheral blood of patients with cancer, including breast cancer (3). Thus, blocking CTLA4 function on T regulatory cells may also result in enhanced immunotherapy.

In patients, CP-675,206 exhibits a biphasic PK profile following IV infusion. The mean systemic exposure parameters (maximum plasma concentrations [Cmax] and area under the plasma concentration-time curve [AUC]) increase with dose in an approximately proportional manner. Based on the data collected from the single dose phase 1 Trial A3671001, CP-675,206 has a low clearance (0.132 mL/h/kg), a small volume of distribution at steady state (81.2 mL/kg), and a long terminal half-life (22.1 days). These values are consistent with those of natural IgG2.

The anti-tumor activity of antibodies to CTLA4 has been demonstrated in a variety of murine tumor models. In 1996, enhancement of antitumor immunity by CTLA4 blockade was shown for the first time in mice. Here, in vivo administration of antibodies to CTLA4 resulted in the rejection of tumors, including pre-established tumors. In addition, this rejection resulted in immunity to a secondary exposure to tumor cells, suggesting that blockade of the inhibitory effects of CTLA4 can allow for, and potentiate, effective immune responses against tumor cells (4).

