## **Dose Escalation Rules**

To minimize the risk of this combination to patients, dosing in the first dose level cohort only will proceed by evaluating safety in the first patient for 12 weeks after the dose of CP-675,206. Prior CP-675,206 single-agent data on safety findings from Pfizer studies indicate that a 6-week follow-up interval was appropriate. However, in order to monitor for potential late-onset toxicities due to the combination of CP-675,206 with radiation, this protocol will follow patients for 12 weeks.

Dosing will be conducted in subsequent dose level cohorts of at least 3 patients, with patients assigned to a dose group after verification by the Investigator of eligibility.

Safety considerations in a current dose level will be assessed as follows to determine dose level escalation:

**1.** If no patient experiences a DLT in the first 12 weeks, the trial will proceed to the next dose level cohort

**2.** If 1/3 patients experiences a DLT in the first 12 weeks, expand cohort to 3 additional patients, and then determine:

- 1. • If 1/6 patients experiences a DLT in the first 12 weeks, escalate to the next dose level.
  2. • If ≥2/6 patients experience a DLT in the first 12 weeks, the current dose level will be considered above the maximum tolerated dose and dose escalation will be discontinued.

**3.** If ≥2/3 patients experience a DLT in the first 12 weeks, the current dose level will be considered above the MTD and the preceding dose level cohort will be expanded to a minimum of 6 patients.

The dose escalation will end after DLT is observed in ≥2 out of 3-6 patients treated at any dose level or after 6 patients at the highest dose level defined (CP-675,206, 15 mg/kg) have completed the 12-week observation period.

Additional patients may be entered as needed at any dose level, including intermediate dose levels, to more fully elucidate the pattern of toxicity and/or better define the MTD.

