## **4.4. Dose Limiting Toxicities**

Adverse events and other symptoms will be graded according to the NCI Common Terminology Criteria for Adverse Events version 3.0. (<http://ctep.cancer.gov/reporting/ctc.html>).

Dose-limiting toxicity (DLT) is defined as any of the following when considered related to CP-675,206 therapy:

1. • Any CTC Grade 4 treatment related toxicity of any duration.
2. • Other Grade 3 or greater toxicities that do not recover to ≤ Grade 1 or baseline within 7 days of maximal management
3. • Grade 2 or greater treatment related clinical autoimmune toxicity of critical organs, which are defined as lung, heart, kidney, bowel, bone marrow and nervous system, including the eye (except anterior uveitis).

Assessment of DLTs during the first 12 weeks after CP-675,206 dosing will be completed to determine the next dose level.

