### **6.1.4. Management of CP-675,206 Toxicity**

CP-675,206 is an immune modulator, so Investigators should be alert for the development of immune-mediated side effects.

The majority of the adverse events reported in early phase trials have been manageable and well tolerated. The most common treatment-emergent, treatment-related adverse event is diarrhea. Diarrhea typically developed 1 to 2 months after the first dose of CP-675,206 (range: 4-72 days).

Although CP-675,206 is a fully human monoclonal antibody, immunogenicity remains a possibility, and thus acute hypersensitivity reactions such as urticaria, pruritus, laryngeal edema, angioedema, bronchospasm, respiratory distress, nausea, vomiting, abdominal cramps and pain, acute back pain, fever, diarrhea, hypotension and fatal anaphylactic shock, as well as sub acute reactions, are also possible. Possible immune-mediated disorders observed involve the skin (vitiligo and cutaneous leukocytoclastic vasculitis), the thyroid gland (autoimmune thyroiditis), the liver (autoimmune hepatitis), the pituitary (hypophysitis) and bone marrow (immune thrombocytopenic purpura). Abnormal lab results that may be immune-mediated include elevations of serum lipase and amylase and liver function tests. There has been one report of treatment-related uveitis, which resolved within 48 hours after treatment with topical steroids. Across all studies, toxicities generally recovered within 12 weeks, allowing continuation of treatment.

If a patient has an adverse event that is thought to be potentially immune-mediated (other than vitiligo), the Investigator should send a blood sample for autoimmune antibody testing.

CP-675,206 is a monoclonal antibody of the IgG2 type, and it is expected that it would cross the placenta if administered to a pregnant woman and could be secreted in breast milk of a lactating woman. The effect of exposure of a fetus or newborn to CP-675,206 is unknown. Women of childbearing potential must agree to use contraception during this trial and for 12 months after the last dose of CP-675,206.

*Note:* In general, it is not expected that the combination of CP-675,206 with this radiation dose will increase CP-675,206-related toxicities. However, radiation of the sites that are the most common autoimmune targets following CP-675,206 administration will be avoided when possible.

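### The protocol sets conflicting periods for observing new toxicity in dosed patients who leave early, so late immune events may go uncollected and it is unclear how these patients count for escalation

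*Protocol*

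**What the plan says.** Safety is what the trial measures: "The primary endpoint will be toxicity" (Section 1). Treatment is a single infusion on the third day of radiation, so nearly every discontinuation follows exposure.

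The protocol gives several answers on how long a dosed patient is observed:

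- **Dose Escalation Rules.** A 6-week interval is described as appropriate for the single agent, but because the combination might cause late-onset toxicity, "this protocol will follow patients for 12 weeks".
- **Section 4.4.** "Assessment of DLTs during the first 12 weeks after CP-675,206 dosing will be completed to determine the next dose level".
- **Patient Withdrawal.** "The final evaluation required by the protocol will be performed at the time of trial discontinuation". What remains is contact about unresolved adverse events, discretionary follow-up, and: "Patients who withdraw from treatment should be followed for survival, and their subsequent treatments should be recorded". Item 3 makes discontinuation compulsory once chemotherapy or biological therapy is judged best for the patient, with no reference to the 12-week window.
- **Section 6.1.5.** For a Grade 2 infusion reaction that recurs on resumption: "If symptoms reappear, stop infusion and discontinue patient from the trial".
- **Section 7.3.1.** One visit is required about 30 days after the end of treatment evaluation. The text concerns ongoing events, with laboratory tests only where clinically warranted.
- **Reporting requirements (Section 9).** Adverse events are followed for 6 weeks after the last dose.
- **Section 4.3.** A patient is MTD evaluable on one dose plus all five fractions. The note beneath it holds escalation until every patient in the cohort has been observed for 12 weeks.

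**The concern.** The 12-week window was chosen because late toxicity was expected. Section 6.1.4 reports: "Diarrhea typically developed 1 to 2 months after the first dose of CP-675,206 (range: 4-72 days"). Section 2.2 gives the antibody "a long terminal half-life (22.1 days"). A patient who leaves in the first weeks is therefore still exposed and still inside the known onset period, but no section clearly requires anyone to look for a new event through week 12.

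Leaving early is foreseeable. This is a metastatic population imaged at 6-8 weeks, inside the DLT window, and a decision to start other therapy triggers discontinuation.

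Two things are at stake. First, Section 10.4.1 characterises adverse events by frequency and timing, and both are biased low if late events in early leavers are not collected. Second, cohorts have 3 to 6 patients, so the way one early leaver is counted can matter to the 0/3 or 1/6 decision.

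**Working it through.** **1. The observation gap.** Let a patient leave t days after the infusion. The sections allow three readings of the last day on which new events are sought:

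- A: both the 6-week period and the 30-day visit cover new events, and the visit runs from the discontinuation evaluation: max(42, t + 30).
- B: only the 30-day visit covers new events: t + 30.
- C: only events already unresolved are pursued: t.

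| Leaves at day t | Last look A / B / C | Days unobserved to day 84, A / B / C | Days unobserved to day 72, A / B / C |
| --- | --- | --- | --- |
| 0 | 42 / 30 / 0 | 42 / 54 / 84 | 30 / 42 / 72 |
| 28 | 58 / 58 / 28 | 26 / 26 / 56 | 14 / 14 / 44 |
| 42 | 72 / 72 / 42 | 12 / 12 / 42 | 0 / 0 / 30 |

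Under A the gap closes for anyone leaving on or after day 54 (84 − 30). For the earliest leavers it opens at day 42 (A) or day 30 (B). Table 2 does not identify the end of treatment evaluation, so the anchor for the 30-day visit is itself uncertain.

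**2. Drug remaining.** Terminal phase only, 0.5^(t/22.1): 0.39 at day 30, 0.27 at day 42, 0.07 at day 84. Section 2.2 describes a biphasic profile, so these are approximate.

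**3. The plan's own escalation table (Section 10.3).** With escalation on 0/3 or 1/6:

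P(escalate) = (1 − p)^3 + 3p(1 − p)^2 × (1 − p)^3

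For p = 10% to 90% this gives 0.906, 0.709, 0.494, 0.309, 0.172, 0.082, 0.032, 0.0088 and 0.001. The printed values 0.91, 0.71, 0.49, 0.31, 0.17, 0.08, 0.03, 0.009 and 0.001 are reproduced. The calculation takes every patient's 12-week DLT status as known.

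**4. Sensitivity if an unobserved patient were counted as DLT-free.** This is an assumption; the protocol does not say it.

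One of the first three unobserved: (1 − p)^2 + 2p(1 − p) × (1 − p)^3

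- p = 30%: 0.49 + 0.42 × 0.343 = 0.63, against 0.49.
- p = 40%: 0.36 + 0.48 × 0.216 = 0.46, against 0.31.

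A share d of patients discontinued before week 12, with a share m of their DLTs unrecorded: replace p by p(1 − d × m). This takes leaving as unrelated to DLT risk. The protocol gives neither d nor m, so a range is shown:

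| True DLT rate | Stated | m = 1; d = 10%, 20%, 33% | m = 0.5; d = 10% to 33% |
| --- | --- | --- | --- |
| 30% | 0.49 | 0.56, 0.62, 0.71 | 0.53 to 0.60 |
| 40% | 0.31 | 0.38, 0.45, 0.56 | 0.34 to 0.43 |

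**The case against.** A reader might infer that safety observation simply stops at discontinuation. The protocol does not support that. The 6-week period in the Reporting requirements runs from dosing, whatever the patient's trial status; Section 7.3.1 requires a visit with a physical examination for signs of autoimmunity; and Patient Withdrawal asks for every effort to document outcome. This stands, and it narrows the gap to the later part of the window in patients who leave early. It does not close it: 6 weeks is the interval that the Dose Escalation Rules deliberately lengthened.

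A reader might also infer that early leavers are recorded as free of late toxicity, or that escalation proceeds on missing data. No section says the first. Against the second, Section 4.3 bars escalation until all patients in the cohort have 12 weeks of observation, and Section 6.1.1 makes the decision wait for the last patient. That safeguard is real. However, it creates no assessments for someone who has left, and it sits beside an evaluability definition with no minimum observation time. Read strictly, a cohort with an early leaver cannot escalate; read loosely, the leaver counts. It also does nothing for adverse event frequency and timing.

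A uniform onset over 4-72 days would turn the gap into a percentage, for example (72 − 42)/68 = 44% for a patient last seen at 6 weeks. Section 6.1.4 says onset was typically at 1 to 2 months, so such a figure is illustrative at most.

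Three further points limit the concern:

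- Section 6.3 asks that other cancer therapy wait 12 weeks where clinically acceptable, which should reduce the number of early leavers.
- Once new therapy starts, attribution is harder, and a DLT must be considered related to the antibody.
- A patient whose infusion is stopped under Section 6.1.5 may not have received the one dose that Sections 4.3 and 10.1 require, so it is uncertain whether that patient enters the analysis.

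**Conclusion.** The point holds as an internal conflict. The clearest clash is 6 weeks of adverse event follow-up against a 12-week toxicity window. Patient Withdrawal adds to it by placing the last required evaluation at discontinuation without preserving the window. Late new-onset toxicity in early leavers may be missed; it is not shown to be missing.

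For a patient leaving at the infusion, 42 to 54 days of the 84-day window lack a clear requirement to look for new events if at least the 30-day visit covers them (readings A and B). The gap shrinks for later leavers, and under reading A it disappears from day 54. The bias in adverse event frequency and timing is downward; its size cannot be given because the protocol states no discontinuation rate.

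The escalation figures (0.49 rising to 0.63 with one unobserved patient among the first three, or to 0.56-0.71 across the assumed discontinuation range with all their DLTs unrecorded, at a true 30% rate) show what is at stake if the counting ambiguity is resolved the wrong way. They do not describe what the protocol prescribes. The printed escalation table is correct. The sections should be reconciled because they bear on the primary endpoint and the repair is cheap.

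**What to change.** - In Patient Withdrawal, separate stopping treatment from ending data collection. Any patient exposed to any amount of CP-675,206 continues the Table 2 safety assessments, or at least adverse event contacts, through 12 weeks after dosing, unless consent to follow-up is withdrawn.
- State that discontinuation, including under Section 6.1.5, does not end this follow-up. This concerns data collection only and leaves the management of the reaction as it is.
- Record the start and type of any new therapy for attribution; starting it does not end adverse event or DLT collection.
- In the Reporting requirements, change the 6-week adverse event period to match the 12-week window. In Section 7.3.1, define the end of treatment evaluation.
- In Section 4.3, state that a patient without a DLT who was not observed to week 12 does not count as DLT-free in the 0/3 or 1/6 decision, and whether that patient is replaced. Section 10.2 already allows for 2 non-evaluable subjects.

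The cost is protocol wording, a few extra visits or calls on a schedule that already exists, and harder attribution of events that follow new therapy.
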